#### Data collection and analysis

Both patient-related (e.g. improvements of care,) as well as payer-related (e.g. hospitalizations, utilization of outpatient care) objectives will be considered in the analysis. With MamBo a mean cost reduction of 12,5% is expected due to reduced hospitalization rates. For all variables, a comparison is made between the intervention group and the twin group with significance tests. The selection of the appropriate statistical test depends, among others, on the type (binary/continuous) and distribution of the respective variables.

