**Methods:**

The MamBo-care model will be evaluated in multi-perspective terms. Thus, a process and outcome evaluation with several data sources will be conducted: (1) Annual focus groups and individual interviews with those involved in the process. (2) Various primary data, including surveys of patients, physicians and practice staff at the time of enrolment and 1 year later to enable pre-post comparison. (3) Claim data from the health insurance of the MamBo population in comparison to a comparative population, formed by the propensity score matching method. (4) Process data of the care management. The analysis of qualitative data will be carried out by content analysis according to Mayring. For the analysis of the quantitative data, multivariate analyses are planned.

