### SHI-claim data

#### Sampling

Claim data will be used to assess and compare the costs and use of health services between MamBo patients and patients in standard care. For this purpose, the SHI “PronovaBKK” provides anonymised claim data of the MamBo-population. A statistical twin with data available to the German Health Risk Institute (HRI) [31] is determined for each MamBo participant using the propensity score matching (PSM) method [32]. Matching is performed by the HRI according to criteria such as age, gender and diagnosis.

A sample size of *n* = 2617 corresponding to a statistical power of 79.2% was aimed, given an unpaired t-test, a Cohen’s d of 0.068 and a significance level of 0.05. However, the patients’ enrolment did not correspond to the expected sample size goals, which caused reduced statistical power. To ensure maximum statistical power, the evaluation design of the SHI-claim data analysis has been adopted to the different temporal availabilities of the key parameters. One part can be delivered within 3 months. The other part is available with a delay of up to 9 months. Therefore, group 1 (*n* = 1.975) was closed on 01.04.2019 and group 2 (*n* = 2365) was closed on 01.10.2019. By this, sufficiently high power is guaranteed. The power for Group 1 is about 68% and for Group 2 about 76%.

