## Discussion

The “MamBo” care model offers a new form of coordinated, managed and cross-sectoral care for multimorbid patients. There are already coordinated programmes such as the DMPs in Germany [7]. While DMPs only promote isolated diseases, MamBo addresses the needs of multimorbid patients. This study evaluates a new form of care formatively and summatively. By conducting a multi-perspective study with several data sources and study results, patient-, provider- and cost-unit-related goals are addressed. In addition, confounding factors are taken into account by considering various additional data sources, such as process data and SHI claim data. As far as we know, the study will also be the first to formatively evaluate the benefits of a management consultancy that supports the change management as an implementation strategy for complex health innovations.

However, it should be noted that this study is a health services research study. Thus, this is an evaluation study that primarily investigates the effectiveness of a new care model. Consequently, the study shows its limitations. There will be an increased risk of selection bias due to the quasi-experimental study design in which participating physicians enroll patients and only selected patients receive MoniKa treatment. Additionally, within the formative evaluation just willing and thus mostly active physicians can be interviewed. Due to difficulties in the recruitment process, the evaluation-design had to be adopted during the project period. The occurrence of group differences between patients who completed the t1 survey after one year and patients who were interviewed after a six-month intervention cannot be completely excluded.

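### The described claims analysis uses no pre-enrolment cost or hospitalisation: a risk of carried-over selection bias and an avoidable loss of power

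*Protocol article*

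**What the plan says.** The claims comparison is described under SHI-claim data in the protocol article.

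- **Matching (Sampling).** A statistical twin "is determined for each MamBo participant using the propensity score matching (PSM) method". The criteria are given as examples: "Matching is performed by the HRI according to criteria such as age, gender and diagnosis".
- **Analysis (Data collection and analysis).** "For all variables, a comparison is made between the intervention group and the twin group with significance tests". The test is to be chosen by, among other things, the type and distribution of the variable. A mean cost reduction of 12.5% is expected.
- **Power (Sampling).** The target was a sample size of "2617 corresponding to a statistical power of 79.2% was aimed", "given an unpaired t-test, a Cohen’s d of 0.068 and a significance level of 0.05". Enrolment fell short, and the data were split into two cuts with different closing dates, Group 1 (n = 1975) and Group 2 (n = 2365): "The power for Group 1 is about 68% and for Group 2 about 76" per cent.

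Three other places bear on the point. The Abstract (Methods) says "For the analysis of the quantitative data, multivariate analyses are planned". The questionnaire section plans difference-in-differences (DiD) with inverse-probability weights for the patient survey. The Discussion concedes: "There will be an increased risk of selection bias due to the quasi-experimental study design in which participating physicians enroll patients".

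**The concern.** Cost and hospitalisation are the payer-side outcomes, and patients of the same age, sex and diagnoses can differ in both before enrolment. A physician who decides whom to enrol may see need that those three criteria do not capture. The obvious safeguard is the patient's own earlier value of the outcome, used in the matching, in the analysis, or in both. The article names it in neither, while the survey receives a baseline-anchored, weighted analysis.

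Two things are at stake. First, the target effect is very small (d = 0.068), so even a modest prior difference that persists after matching is large relative to it. Second, the earlier value of an outcome usually predicts the later one, so a test that ignores it has more residual variance than it needs. That matters in a comparison which the article itself says has lost power through low enrolment.

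**Working it through.** **Inputs from the article:** d = 0.068; alpha 0.05; unpaired t-test; one twin per participant, so n is read as per group; n = 2617 (target), 1975 (Group 1), 2365 (Group 2). Table 1 gives about 2524 for Group 2; 2365 is used because the stated power is attached to it.

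**Inputs assumed, not in the article:** r, the within-group correlation of pre- and post-enrolment cost after matching, 0.3 to 0.6; b, the pre-enrolment imbalance left after matching, 0.02 or 0.05 SD; equal SD before and after enrolment.

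**Step 1: reproduce the stated power.** Power = Φ(d·√(n/2) − z).

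| n per group | d·√(n/2) | One-sided 0.05 (z = 1.645) | Two-sided 0.05 (z = 1.960) | Stated |
|---|---|---|---|---|
| 2617 | 2.460 | 79.2% | 69.1% | 79.2% |
| 1975 | 2.137 | 68.9% | 57.0% | about 68% |
| 2365 | 2.338 | 75.6% | 64.7% | about 76% |

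The stated figures reproduce only with a one-sided 5% level. The article does not state sidedness, so both bases are shown below.

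**Step 2: power with baseline adjustment.** Adjusting for the pre-enrolment value multiplies the residual SD by √(1 − r²), so the effect in SD units becomes d/√(1 − r²). Example, Group 1 at r = 0.5: 2.137/0.866 = 2.467, and Φ(2.467 − 1.645) = 79.5%.

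| r | Group 1 one-sided | Group 1 two-sided | Group 2 one-sided | Group 2 two-sided |
|---|---|---|---|---|
| plain test | 68.9% | 57.0% | 75.6% | 64.7% |
| 0.3 | 72.4% | 61.0% | 79.0% | 68.8% |
| 0.5 | 79.5% | 69.4% | 85.4% | 77.0% |
| 0.6 | 84.8% | 76.1% | 89.9% | 83.2% |

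The variance falls by r², that is by 9% to 36%. In Group 1, 1975 pairs then carry the information of 1975/0.91 = 2170 to 1975/0.64 = 3086.

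**Step 3: change score (plain DiD).** Its SD is √(2(1 − r)) times the outcome SD. At r = 0.3 the factor is 1.183, and Group 1 power falls to 56.4% one-sided (43.9% two-sided). At r = 0.5 the factor is 1 and power equals that of the plain test. Below 0.5 it is less precise than the planned test.

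**Step 4: bias if prior cost is unbalanced.** A comparison that ignores baseline carries a bias of r·b (in SD), which shifts the test statistic by r·b·√(n/2).

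- b = 0.02, r = 0.3: bias 0.006 SD, 9% of d. Shift 0.189 (Group 1) and 0.206 (Group 2); two-sided type I error 5.4% and 5.5%.
- b = 0.05, r = 0.5: bias 0.025 SD, 37% of d. Shift 0.786 and 0.860; two-sided type I error 12.3% and 13.8%.

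On a one-sided 5% level, with the imbalance in MamBo's favour, the same two cases give 7.3% and 7.5%, and 19.5% and 21.6%. If matching balances prior cost, b is about zero and so is this bias.

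For scale only: if d = 0.068 stands for the 12.5% saving, which the article does not say, SD/mean is 0.125/0.068 = 1.84. Then 0.02 SD is about 3.7% of mean cost and 0.05 SD about 9.2%.

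**The case against.** The strongest reply is that a condensed article is being read as if it were complete. The matching criteria are introduced as examples, so prior cost may already be in the propensity score, and the full variable list properly belongs in the full protocol or analysis plan. Nothing describes the claims comparison as unadjusted: matching is itself the planned control for confounding, and the choice of test is left partly open. The abstract promises multivariate analyses, which suggests that the claims section is an abbreviation. Table 1 says when claims data are collected, not which period they cover. The Discussion discloses the selection risk. The size of any bias rests on a correlation and an imbalance that the article does not give, and small values do little harm.

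Most of this stands, and it limits the point. A reader might infer that the trial runs a purely post-enrolment, unadjusted comparison and that prior cost differences do pass into the MamBo effect. The text does not support that: the list is open, the claims period is unstated and no imbalance is shown. Nor does the abstract's general sentence prove a contradiction.

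What the reply does not do is point to a baseline-adjusted claims analysis anywhere in the article. The specific text names group tests and powers them on an unpaired t-test, and the regression, DiD and weighting are described in the questionnaire section. Disclosing selection does not control it. The power argument also does not depend on what was matched.

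**Conclusion.** The point holds as a risk of bias together with an avoidable loss of power.

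- **Bias:** conditional on matching leaving prior cost unbalanced. Within the assumed range it runs from negligible (two-sided type I error about 5.5%) to material (12% to 14%). The article does not settle which applies, so it cannot be reported as an established bias.
- **Power:** firmer, because it holds whether or not prior cost is matched. It rests on the assumed post-matching correlation of 0.3 to 0.6. On the one-sided basis that reproduces the article's figures, the gain is about 3.5 to 16 points in Group 1 (68.9% to 72.4%-84.8%) and 3.4 to 14 points in Group 2 (75.6% to 79.0%-89.9%). Two-sided, Group 1 goes from 57% to 61%-76% and Group 2 from 65% to 69%-83%. A weaker correlation would give a smaller gain.

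**What to change.** 1. For cost and utilisation outcomes, replace the plain group test with a regression of the post-enrolment outcome on group, adjusted for the pre-enrolment value of the same outcome. State the pre- and post-enrolment periods.
2. State whether pre-enrolment cost and hospitalisation enter the propensity score, and add them if they do not.
3. Report pre-enrolment cost and hospitalisation in both groups as a balance check.
4. Keep a change-score DiD as a sensitivity analysis only, because it loses power when the correlation is below 0.5.
5. Align the claims section with the abstract's statement on multivariate analyses.

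The cost is one earlier period of claims from the existing data holders, a rule for members without full prior insurance coverage, and a few lines of analysis plan. The article does not show that the earlier claims are available, so this must be confirmed. No additional patients are needed.

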### RGL process data (physician’s network)

The number of participating physicians and of patients they enroll, all processes of the CM including activities of the MoniKa and the number and contents of the continuous improvement process meetings are documented in the RGL. This data is handed in quarterly to the evaluating institute in aggregated form. This data enables the evaluation of the success of the implementation determined by successful MoniKa delegation, quality and quantity of MoniKa visitations and sustainable physicians’ participation.

## Discussion

The “MamBo” care model offers a new form of coordinated, managed and cross-sectoral care for multimorbid patients. There are already coordinated programmes such as the DMPs in Germany [7]. While DMPs only promote isolated diseases, MamBo addresses the needs of multimorbid patients. This study evaluates a new form of care formatively and summatively. By conducting a multi-perspective study with several data sources and study results, patient-, provider- and cost-unit-related goals are addressed. In addition, confounding factors are taken into account by considering various additional data sources, such as process data and SHI claim data. As far as we know, the study will also be the first to formatively evaluate the benefits of a management consultancy that supports the change management as an implementation strategy for complex health innovations.

However, it should be noted that this study is a health services research study. Thus, this is an evaluation study that primarily investigates the effectiveness of a new care model. Consequently, the study shows its limitations. There will be an increased risk of selection bias due to the quasi-experimental study design in which participating physicians enroll patients and only selected patients receive MoniKa treatment. Additionally, within the formative evaluation just willing and thus mostly active physicians can be interviewed. Due to difficulties in the recruitment process, the evaluation-design had to be adopted during the project period. The occurrence of group differences between patients who completed the t1 survey after one year and patients who were interviewed after a six-month intervention cannot be completely excluded.

## Data Availability

It is planned to submit the results of the formative and summative evaluation for publication in peer-reviewed journals and to present them at national and international conferences. The dissemination will also be supported by professional public relations activities. The anonymous datasets generated during the current study may be made available from the corresponding author on a reasonable request. Protocol modifications will be communicated to relevant parties.

## Abbreviations

CM: Care Management
CIP: Continuous Improvement Process
DM: Demand Management
DiD: Difference-In-Differences
DMP: Disease Management Programme
GP: General Practitionairs
HRI: German Health Risk Institute
IPW: Inverse-Probability Weights
MoniKa: Monitoring and Coordinating Assistant
MamBo: People with Multimorbidity in Outpatient Care: Patient-Focused and Needs-Oriented Healthcare Management”
PSM: Propensity Score Matching
RGL: Regional Health Network
SHI: Statutory Health Insurance
SEM: Structural Equation Modeling
